**Table 2 T2:**
[figure not shown]
Definitions of consensus.

Round 3

In round 3, only participants who have responded to at least 40% of the outcomes in the round 2 will be eligible to continue the survey. Participants will see the outcomes included by the round 2 survey, including the number of participants scored and score distribution for each outcomes. The 9-point Likert-scale will be used again. And this round survey also requires completion within 3 weeks.

If an outcome still scored “critical” by more than 70% of participants from any stakeholder group and “limited importance” by less than 15% of participants from any stakeholder group (See detail in Table 2), it will be carried forward for face-to-face meeting. All statistical analysis processes will require the same as the round 2.

#### Face-to-face meeting

2.5.2

The purpose of this face-to-face meeting is to discuss the divergent outcomes in the round 3 of Delphi survey, and to verify and agree on the list of final outcomes that constitute COS. If they still disagreements on some outcomes, they will resolve it by voting. Similar to the Delphi stage, outcomes will be considered as “consensus in” if 70% of the consensus meeting participants votes in favors of the outcomes to be included in the COS. The planned meeting time is half a day. In order to achieve effective consensus, the participants consist of 2 parts: 1 facilitator and 13 stakeholders. The facilitator will not be able to participate in the discussion. Firstly, these stakeholders whom must complete all rounds of the Delphi study. The 13 stakeholders in this study will be distributed as follows: 4 patients, 4 clinicians, 4 researchers, and 1 policy-makers. All participants will be paid a certain amount, such as travel expenses and accommodation fee.

### Selection of instruments for each final COSs

2.6

Following completion of the identification of final COSs, 2 reviewers will systematically review the instruments for each final COSs in clinical trials for OSAHS. If the outcome only has 1 instrument, then this instrument is the final instrument. If there are multiple instruments for a outcomes, the identified outcome instruments will be evaluated according to the 9 measurement properties identified by the COSMIN initiative:^[19]^ Internal consistency, reliability, measurement error, content validity, structural validity, hypotheses testing, cross-cultural validity, criterion validity, and responsiveness. The instrument with the highest score will be selected.

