Early recognition and appropriate therapy are the primary options for managing the disease.^[8]^ The overnight polysomnogram is the standard diagnostic test for OSAHS.^[6]^ It can simultaneously record multiple physiological signals during sleep, such as electroencephalogram, electrooculogram, electromyogram, oronasal airflow, and oxyhemoglobin saturation. As a chronic disease, the treatment of OSAHS is mainly to relieve upper airway obstruction, and needs to education and follow up patients continuously, and adjust the treatment strategy in time to ensure the efficacy.^[9]^ Lifestyle modifications, such as weight loss, alcohol sedative-avoidance, smoking cessation, avoidance of sleep deprivation, will decrease both the symptoms of OSAHS and the comorbid conditions.^[7,10]^ In addition, Chinese medicine has also become an effective treatment for OSAHS.^[11,12]^ All in all, there have been an increasing number of clinical trials of OSAHS in recent years. However, like clinical trials in other fields,^[13–15]^ the clinical trials of OSAHS also have heterogeneous outcomes, surrogate outcomes, subjective outcomes, and composite outcomes, as well as lack of endpoints or patient perspectives.

The best method to improve the reporting of outcomes is to develop a core outcomes sets (COSs), that is, the minimum set of outcomes in which all studies in a particular situation are scientifically agreed and reported.^[16]^ The COSs must be measurable and relevant. Involving patients and other key stakeholders are the key to achieving relevance. Studies have shown that the COS can make the reporting of outcomes of the study more standardized.^[17,18]^ With the Core Outcome Measures in Effectiveness Trials (COMET) Initiative founded and committed to the development, implementation, dissemination and update of COSs by published the consensus-based standards for the selection of health measurement instruments (COSMIN), the development and implemented of COSs has become an inevitable trend.^[19]^

To date, there is currently no available COSs for OSAHS's clinical trials. The first aim of this study is to develop a COS for OSAHS's clinical trials. The second aim is to select a measurement instrument for each outcome included in the COSs with the method recommended by the COMET initiative after completing the COSs. Finally, we will focus on the promotion of this COSs.

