## Methods

2

The development of this COS follows COMET and COS-standard for Development core outcomes sets -standard for developmerecommendations.^[19,20]^ At the same time make appropriate adjustments according to the actual situation. After completing the registration, there are 5 stages:

(1)set up a Steering Group, defining the scope of this COSs;(2)identifying potential core outcomes by systematic review and semi-structured interviews;(3)identifying final COSs by consensus process, includes Delphi survey and face-to-face meeting;(4)identification and evaluation of instruments used to measure the final COSs;(5)promotion and updates. See detail in Figure 1.

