#### Delphi survey

2.5.1

We will use a Delphi survey to develop consensus on the core outcomes from those identified in the systematic reviews and semi-structured interviews. The advantage of this technique over a roundtable meeting is that it avoids situations where some people can lead the discussion or situations where other individuals feel obligated to agree with the opinions of more senior members. In order to improve efficiency, the questionnaire will be completed online using appropriate online survey design software.^[21]^ A minimum of 3 Delphi rounds is planned. There is currently no standard sample size calculation method in the Delphi process, but our goal is a total of 180 participants, including at least 30 patients (Confirmed cases from tertiary hospitals aged over 18 with a history of more than 3 years.).^[22]^ We will strive to increase the response rate of the participants.

The participants are all stakeholders. In addition to patients, we plan to include the following 3 groups of people:

(1)clinicians: respiratory physician, cardiologist, otolaryngologist, general practitioner, doctor of traditional Chinese medicine, nurse;(2)researchers: experts in respiratory diseases at domestic and foreign medical schools, respiratory specialists in various research institutions;(3)policy-makers: national, provincial, municipal, county, and other levels of health management personnel, some health policy-makers outside of China will also be invited. Potential participants will determine whether they are willing to participate in the Delphi survey via email or phone.

A preliminary list of potential outcomes will be produced by reviewers, and will be reviewed by the Steering Group. Participants are asked to evaluate the importance of the listed items. Participants can also choose to add other items they think are missing and score each item added. The detailed process will proceed as following.

Round 1

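### A sole instrument is made final without appraisal, and several are ranked with no minimum standard and no option to select none

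*Protocol article*

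**What the plan says.** The Introduction gives as the second aim to "select a measurement instrument for each outcome included in the COSs with the method recommended by the COMET initiative". The Methods overview lists five stages, and the fourth is "identification and evaluation of instruments used to measure the final COSs".

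Section 2.6 (Selection of instruments for each final COSs) sets out how this is done. Two of the study's reviewers systematically review the instruments used in OSAHS clinical trials for each core outcome. Two cases follow:

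- **One instrument found:** "If the outcome only has 1 instrument, then this instrument is the final instrument".
- **Several found:** "the identified outcome instruments will be evaluated according to the 9 measurement properties identified by the COSMIN initiative". The properties are "Internal consistency, reliability, measurement error, content validity, structural validity, hypotheses testing, cross-cultural validity, criterion validity, and responsiveness". Then: "The instrument with the highest score will be selected".

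The section gives no scale or weights for the score, no minimum score, and no property that an instrument must satisfy. It does not provide for the result that no instrument is adequate.

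**The concern.** Appraisal depends on how many instruments the review finds, and that number says nothing about quality. The pool consists of tools that have been used in OSAHS trials, and use in a trial is not evidence of validity or reliability. An outcome may have only one tool because little measurement work has been done on it. In that case the check is missing where it is most needed.

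Where there are several tools, appraisal takes place but serves only to order them. The best of a weak group is recommended in the same way as the best of a strong group.

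The second aim is at stake. Section 2.7 plans to spread the result through publications, conferences, professional societies and the COMET database. A tool with poor or untested properties would carry the same recommendation as a well-supported one, and trialists could not tell them apart.

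**Working it through.** No sample size, power or error rate is involved, so the check is a reading of the decision rule against the rest of the article.

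**Inputs**
- Single-instrument rule, several-instrument rule and list of properties: section 2.6.
- Description of stage 4: Methods overview.
- Second aim: Introduction.
- Possible safeguards elsewhere: sections 2.2, 2.4, 2.5 and 2.8.

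**Step 1. The list.** Counting the properties named in section 2.6 gives nine, which agrees with the stated nine. There is no error here.

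**Step 2. One instrument.** The appraisal is introduced under the condition that there are multiple instruments. With one, the text goes straight from identification to selection. The Methods overview promises identification *and* evaluation for the final set, with no exception. For a single-instrument outcome the second half of stage 4 is therefore not carried out. The two passages do not agree.

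**Step 3. Several instruments.** Write the scores of the k candidates as s1, ..., sk. The rule selects the candidate with the largest s. For any k of 2 or more a largest value always exists (ties aside), so the rule always returns an instrument. Subtract the same amount from every score and the selection does not change. The rule therefore responds to differences between candidates and not to their level. This holds for any scale and any weights, so it needs no assumption about how the nine properties are scored.

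**Step 4. The two cases together.** Whenever at least one instrument is found, section 2.6 ends in a recommendation. A finding that none is adequate cannot arise under the stated rule.

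**Step 5. A safeguard elsewhere?**
- Section 2.2 says that the Steering Group and fellows are contacted on key decisions in general, and does not mention instruments.
- The specific Steering Group reviews in sections 2.4 and 2.5 concern outcome terms and domains, outcomes raised in interviews, the Delphi list, and disagreements in analysing the Delphi responses.
- Section 2.8 foresees revision and new instruments later, after promotion has begun. It sets no check before an instrument is recommended.

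None of these supplies the missing appraisal or the missing minimum.

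**The case against.** The strongest reply is that this is a condensed article. Scoring rules, weights and the treatment of properties that do not apply may stand in a fuller protocol, and the Introduction refers to a COMET-recommended method that is not reproduced. That reply has force for the details of scoring. It does not remove the single-instrument rule, which is stated outright: a later check on sole instruments would contradict the word that makes them final. Nor does it change the wording of the several-instrument rule, which is relative as printed. What the cited guidance requires cannot be used on either side, since it is not in the documents.

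Three stronger readings are tempting, and the documents do not support them.

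- *Good marks on other properties will outweigh failed content validity.* This needs an equal-weight, unconditional sum. The article speaks of a highest score and gives no scale or weights, so any worked score would be invented.
- *Physiological measures are handicapped against questionnaires.* Ranking is within one outcome, so the two types compete only if both measure the same core outcome. No core outcome has yet been chosen. Which of the nine properties apply to a physiological index is also not stated.
- *The Introduction's demand that the set be measurable and relevant is breached.* That sentence concerns the outcomes, and the one after it ties relevance to involving stakeholders. It sets no standard for instruments.

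It is also fair to say that section 2.8 leaves a poor choice open to revision, and that the article does not show that any core outcome will have only one instrument.

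**Conclusion.** The point holds in a limited form. Section 2.6 exempts sole instruments from the evaluation that stage 4 announces. Where there are several, it selects the top scorer with no minimum and no option of selecting none. An instrument with poor or unknown measurement properties *can* therefore be recommended; the documents do not show that one *will* be.

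The single-instrument branch is the firmer half, because it rests on an explicit rule and on a mismatch within the article. The several-instrument half rests on the rule as printed and on the assumption that no unseen document adds a minimum standard.

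The number of outcomes affected cannot be estimated, as neither the core outcomes nor their instruments are known yet. The defect weakens the second aim and leaves the development of the core outcome set untouched. It should be corrected before instrument selection begins.

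**What to change.** Revise section 2.6 in three respects.

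1. Apply the same nine-property appraisal to every identified instrument, including one that is the only instrument for its outcome. This brings the section into line with stage 4.
2. Fix a minimum standard before any instrument is appraised, and use the highest score only to choose among those that meet it. One possible form is that there is no evidence of inadequate content validity or reliability, where the property applies to that type of measure. The standard should also say how an instrument with no evidence at all is treated, because a condition worded only in terms of evidence of inadequacy would let it through.
3. If no instrument meets the standard, report 'no instrument recommended yet' for that outcome.

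The cost is one extra appraisal per single-instrument outcome, done by the same two reviewers of the study, plus the work of defining the threshold and stating to which types of measure each property applies. The drawback is that some core outcomes may be published without a recommended instrument, so the second aim would not be fully met for them at first. Section 2.8 already provides for adding instruments later.

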### Update

2.8

As we all know, as medical research continues, understanding of disease, diagnosis, treatment, and evaluation will be updated. Therefore, the COSs of OSAHS also needs constant evaluation and upgrading in accordance with the latest achievements of clinical research. In the promotion process, it is necessary to pay attention to the shortcomings of the COSs of OSAHS at any time. It should then be revised in accordance with standard procedures based on the number and importance of these shortcomings. Only by continuously adding new outcomes and new instruments can we ensure the practicality and advancement of the COS of OSAHS.

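### A sole instrument for a core outcome becomes final without any required assessment of its measurement properties

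*Protocol article*

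**What the plan says.** The Introduction gives the second aim as to "select a measurement instrument for each outcome included in the COSs with the method recommended by the COMET initiative". The Methods list five stages, and the fourth is "identification and evaluation of instruments used to measure the final COSs".

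Section 2.6 (Selection of instruments for each final COSs) sets out that stage. Once the core outcomes are settled, "2 reviewers will systematically review the instruments for each final COSs in clinical trials for OSAHS". The path then splits:

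- One instrument found: "If the outcome only has 1 instrument, then this instrument is the final instrument".
- Several found: "If there are multiple instruments for a outcomes, the identified outcome instruments will be evaluated according to the 9 measurement properties" taken from COSMIN, and then "The instrument with the highest score will be selected".

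Section 2.8 (Update) foresees later revision of the set, in general terms: "Only by continuously adding new outcomes and new instruments can we ensure the practicality and advancement of the COS of OSAHS".

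**The concern.** That only one instrument has been used for an outcome in OSAHS trials says nothing about whether it is valid, reliable or responsive. The protocol names nine properties as its standard for judging instruments, then waives them where there is no competitor. Being the only candidate is treated as being good enough.

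At stake is the credibility of the recommendation. The set is to be promoted through publications, conferences, professional societies and the COMET database (section 2.7), for trials of various interventions (section 2.3). A sole instrument listed there looks the same to a user as one that came through the nine-property evaluation. A reader could not tell a tested instrument from an untested one, and the signal that validation work is needed would be lost.

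**Working it through.** No figure is stated and no arithmetic is needed beyond a count. The check reads section 2.6 as a decision tree and then looks through the rest of the article for anything that would close the gap.

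**Step 1. The two branches.**

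| Instruments found | Properties that must be assessed | Result |
|---|---|---|
| One | 0 of 9 | Accepted as final |
| Two or more | 9 of 9 | Highest scorer selected |

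The evaluation is worded as conditional on there being several instruments. In the first branch the word *final* leaves no later step.

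**Step 2. Against the stage list.** The Methods describe the stage as "identification and evaluation of instruments used to measure the final COSs". Nothing there limits evaluation to outcomes with competing instruments. Section 2.6 delivers identification for every outcome, but evaluation only for some.

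**Step 3. Other places that might supply the missing check.**

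- The systematic review of instruments in section 2.6 covers every outcome, but the article attaches no appraisal criterion to it. The property assessment appears only in the several-instrument sentence.
- The face-to-face meeting (section 2.5.2) decides which outcomes are core. It comes before instrument selection and does not deal with instruments.
- Section 2.8 provides for revision once promotion is under way. It is not a check before an instrument is recommended.

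**Step 4. Consequence.** Take a sole instrument with poor reliability, or one whose content validity has never been studied. In the first branch it is accepted, and no step before publication would require the weakness to be looked for or reported.

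**Step 5. Reach.** The share of outcomes affected would be the number with one instrument divided by the number of core outcomes. The article gives neither, and both depend on work not yet done, so no percentage can be put on it.

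**The case against.** The strongest case on the other side has five parts.

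- *Evaluation would not change the choice.* With no competitor identified, assessment cannot lead to a different instrument. This is right, and it limits the harm. What assessment can change is the status of the recommendation: supported, provisional or withheld. That difference matters to users, so the point survives in this narrower form.
- *The stage list is only a label.* The Methods allow adjustment to circumstances, and evaluation does take place in one branch. The mismatch is therefore a tension rather than a flat contradiction. The explicit sentence in section 2.6 carries the point without it.
- *A condensed article leaves detail to the full protocol.* That does not answer this point, which rests on a stated rule and not on silence. A fuller document that assessed sole instruments before accepting them would contradict the sentence.
- *Some of the nine properties do not apply to every instrument.* True; internal consistency, for example, has no meaning for a single physiological reading. The answer is to assess the applicable ones.
- *Updating will correct mistakes.* It may limit lasting harm, but only after the endorsement has been issued.

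Some stronger readings are tempting and are not supported. A reader might infer that the several-instrument branch is equally defective because no minimum score is given. The article does not show the scoring scheme, and a threshold is the sort of detail a full protocol may hold. A reader might also take "The COSs must be measurable and relevant" as a standard that the rule breaks, but that is a general remark about core outcome sets and sets no requirement for instruments. Nor can a departure from COMET or COSMIN guidance be claimed, since neither source is at hand.

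**Conclusion.** The point holds: section 2.6 lets a sole instrument be endorsed with none of the nine listed properties required to be assessed, and no other part of the article makes good the omission before publication. It should be fixed, but it is not a fatal defect. It bears on the second aim alone; the Delphi results, the meeting vote and the list of core outcomes are untouched, and the rule can be changed at any time before instrument selection begins.

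A reader might infer that measurement error would be built into every later trial that adopts the set. The documents do not support that. The branch applies only where a single instrument is found, that instrument may turn out to be sound, and the number of such outcomes is unknown and could be zero. The conclusion assumes only that section 2.6 will be followed as written.

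**What to change.** In section 2.6:

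1. Delete the sentence that accepts a sole instrument automatically.
2. Have the same two reviewers assess every identified instrument, sole or competing, against those of the nine listed properties that apply to it, and report the result for each outcome.
3. Where the evidence for a sole instrument is insufficient, publish the outcome as core and mark the instrument *provisional, validation needed*, or state *no instrument recommended yet*.

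This brings section 2.6 into line with the stage list and uses criteria the protocol already names. The investigators would set what counts as sufficient evidence; the article offers no basis for fixing a particular threshold here. The cost is a short wording change, a little more reviewer work for outcomes with one instrument, and the possibility that some core outcomes appear without a firm instrument. Where evidence is lacking, that is the accurate thing to report.

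### Section 2.6 takes the highest-scoring instrument with no minimum standard and no priority for content validity, so a tool that does not measure the agreed outcome can be selected

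*Protocol article*

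**What the plan says.** Instrument selection is stage 4 in the Methods overview, described there as "identification and evaluation of instruments used to measure the final COSs". The Introduction gives the aim: to "select a measurement instrument for each outcome included in the COSs with the method recommended by the COMET initiative". The working rules are in section 2.6 and have three parts.

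- **One instrument found.** "If the outcome only has 1 instrument, then this instrument is the final instrument". No evaluation is attached.
- **Several instruments found.** "the identified outcome instruments will be evaluated according to the 9 measurement properties identified by the COSMIN initiative". The list is: "Internal consistency, reliability, measurement error, content validity, structural validity, hypotheses testing, cross-cultural validity, criterion validity, and responsiveness". Content validity is fourth, with no weight, rank or required level.
- **Decision.** "The instrument with the highest score will be selected".

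The section does not say how the ratings are coded or combined, how a property with no evidence is treated, or what happens if every candidate is poor. No other section sets an acceptance level for instruments.

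**The concern.** Content validity differs in kind from the other eight properties. It asks whether the tool measures the outcome the panel agreed on. Good internal consistency or reliability in a tool that measures something else does not repair that failure. A rule that only looks for the maximum treats content validity as one item among nine and lets the others make up for it.

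The protocol is stricter about outcomes than about instruments. In section 2.5.1 an outcome must be rated critical by more than 70% and of limited importance by less than 15%, and in 2.5.2 it needs 70% of the votes. Instruments face no such floor. The Introduction bases the relevance of the set on stakeholder input ("Involving patients and other key stakeholders are the key to achieving relevance"). That sentence is about outcomes and does not contradict 2.6, but it shows what an instrument without content validity would fail to carry through. At stake is a published recommendation that trials use a tool which does not capture the named core outcome.

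**Working it through.** The plan gives no figure to reproduce, because 2.6 has no scale, weight or cut-off. The check therefore asks what the rule permits.

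**Input from the document:** nine properties; the highest score is selected; no minimum stated.

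**Assumptions, not in the document:** equal weights; each property scored 0 or 1, with missing evidence scored 0. A scale of -1, 0, +1 is used as a variant.

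**Step 1, single comparison.** Instrument A fails content validity and passes the other eight: 0 + 8 = 8. Instrument B passes content validity and six of the other eight: 1 + 6 = 7. The rule selects A.

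**Step 2, how often the pattern allows this.** Let a and b be the numbers of the other eight properties that A and B pass. A scores a and B scores 1 + b, so A wins outright when a ≥ b + 2. There are 2^16 = 65,536 patterns. The winning count is the sum of C(8,a)·C(8,b) over a ≥ b + 2. Replacing b by 8 - b turns this into the sum of C(16,k) for k = 10 to 16:

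8,008 + 4,368 + 1,820 + 560 + 120 + 16 + 1 = 14,893

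14,893 / 65,536 = 22.7%. Ties (a = b + 1) number C(16,9) = 11,440, or 17.5%.

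**Step 3, sensitivity to the assumed coding.**

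| Assumption on the other eight properties | A selected outright | Tie |
|---|---|---|
| 0/1, independent, P(pass) = 0.3 | 20.5% | 18.7% |
| 0/1, independent, P(pass) = 0.5 | 22.7% | 17.5% |
| 0/1, independent, P(pass) = 0.7 | 20.5% | 18.7% |
| -1/0/+1, all patterns equally likely | 22.3% | not computed |

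**Step 4, could weighting remove the problem?** On the 0/1 scale, give content validity weight w. The weakest B that passes it scores w, and the strongest A that fails it scores 8. A failing tool can never win only if w > 8, that is, if content validity outweighs the other eight together. That is an entry condition under another name, and 2.6 states neither.

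**Step 5, the missing floor.** Whatever the scoring, a non-empty set of candidates has a highest score. If all are inadequate, the rule still returns one of them. This step needs no assumption about coding.

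**The case against.** The strongest reply is that 2.6 speaks of a highest score, not a total, and gives no coding. A weighted or gated score would also fit the words. The Introduction refers to a COMET-recommended method, 2.6 cites a source for the nine properties, and an article may leave scoring detail to the full protocol. This stands in part. The sum is an inference, and the percentages above describe an assumed scheme in which the eight other properties vary independently. They show that one property can be traded for others; they do not predict what will happen in this study. The reply does not remove the point, because the article does not defer the decision: it states the final rule, and that rule has no floor. What the cited method requires cannot be judged from this document.

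A reader might go further and infer two things that the text does not support.

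- **That the score rewards older or more studied instruments.** The article does not say how absent evidence is scored. On a -1/0/+1 scale, a further study of a property already rated adequate adds nothing, and an unfavourable first study lowers the score.
- **That a poor choice of instrument undoes the consensus work.** The Introduction and Discussion separate what to measure from how to measure it, so the agreed outcome list stands whichever tool is recommended. Section 2.8 also provides for later revision and for new instruments.

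**Conclusion.** The point holds in a limited form. As written, 2.6 can endorse an instrument that fails content validity over one that passes it, and it must endorse something even when every candidate is inadequate. The first part rests on an equal-weight sum, where 8 of 9 beats 7 of 9 and about 20% to 23% of the enumerated comparisons go the wrong way before ties. The second part holds under any scoring. A sole instrument has the same gap in plainer form, since it is accepted unexamined. The agreed outcome list is unaffected; the weakness is confined to the instrument recommendation. The change is cheap and should be made before stage 4 begins.

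**What to change.** Reword section 2.6 so that selection runs in this order:

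1. Appraise content validity for the agreed outcome in every identified instrument, including a sole one.
2. Set aside any instrument whose content validity is not adequate.
3. Compare scores only among those that remain; a sole instrument that passes is accepted.
4. If none remains, report that no instrument can yet be recommended for that outcome.

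With step 2 in place, a failing instrument cannot displace a passing one, whatever the scoring. For competing instruments the change uses ratings that the protocol already plans to collect. The added work is the content-validity appraisal of sole instruments, which 2.6 now omits. The drawback is that some core outcomes may have no recommended instrument for the time being; section 2.8 already allows instruments to be added later.
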